### 9.1.2 Aim 1 Sampling and Analytical Technique

Aim 1 is to enumerate and characterize camps where young men at risk for HIV acquisition and transmission socialize in Dar es Salaam using the PLACE methodology.

**Primary analysis.** A list of camps in the four wards within Dar es Salaam will be collected through Community Informant interviews. A minimum of 450 interviews will be conducted with individuals located in the four wards of focus in Dar es Salaam. Research assistants will systematically move through each *mtaa* (street) in the ward to cover sufficient geographical space in each ward. Research assistants will return to each camp mentioned by community informants to verify whether or not it exists; if found to exist, camp characteristics and GPS coordinates will be collected. Frequencies of camp characteristic categories will be analyzed with SAS SURVEYLOGISTIC version 9.2.

### 9.1.3 Aim 2 Sampling and Analytical Technique

Aim 2 is to determine whether men in camps randomized to receive a microfinance and health leadership intervention have a lower prevalence of sexually transmitted infections (NG, TV, CT) and report perpetrating less physical or sexual violence against female sexual partners as compared to men in camps not randomized to receive the intervention.

Data gathered from cluster randomized studies such as this one are correlated by common group membership and therefore will be analyzed using methods appropriate to such designs. Since all male camp members in selected camps will be eligible for inclusion (p=1.0), a simple random sample of camps with randomization based upon an equal probability method will be conducted. Sampling weights will be computed as the inverse of probabilities of selection with non-response weights over each wave computed as the inverse of response rates. We will compare odds ratios across group at the 12 month assessment for behavioral outcomes and at 30 months for both behavioral and STI outcomes using SAS SURVEYLOGISTIC version 9.2 to incorporate both the complex nature of sample selection and weighting. Controls for covariates will also be introduced where necessary.

### 9.1.4 Mediation Sampling and Analytical Technique

In the event that program effects are identified, we will estimate path coefficients in multiple mediator models and generate bootstrapped confidence intervals for total and specific indirect effects of one or more mediator models using the Mplus program Version 6.11.([Pituch, Stapleton, & Kang, 2006](#_ENREF_65)) We will assess simple and multiple mediation in the relationships between the microfinance intervention condition, intervention mediators including hope, future orientation, social cohesion, social support, emotional distress, gender equity, conflict, alcohol and drug use, HIV stigma, perceived social support, collective efficacy, sexual relationships and risk behavior, attitudes towards HIV risk and intimate partner violence, work and expenditures, sexual relationships and risk behavior, and social and sexual network norms.

## 9.1.5 Treatment of Missing Data

We will examine the pattern of missingness due to loss to follow-up and apply an appropriate multiple imputation strategy if deemed necessary.([Schafer, 1997](#_ENREF_79); [Trials, 2010](#_ENREF_94)) We will use the propensity score method for multiple imputation and the Markov chain Monte Carlo approaches to multiple imputation of binary outcome data.([Rubin & Schenker, 1986](#_ENREF_75)) We will conduct sensitivity analyses that quantify the robustness of inferences to departures from underlying assumptions.([Molenberghs & Kenward, 2007](#_ENREF_56); [Molenberghs, Verbeke, Thijs, Lesaffre, & Kenward, 2001](#_ENREF_57); [Trials, 2010](#_ENREF_94)).

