# 9. STATISTICAL CONSIDERATIONS

## 9.1 Quantitative Statistical Analysis Plan

## 9.1.1 Sample Size, Power Calculations and Effect Size

The choice of 60 camps randomized into two groups is based upon evidence generated in our previous study and likely incidence estimates available from published studies with similar populations in Tanzania and other countries in Africa. We estimate average camp sizes of 36.2 sexually active males and 52 total males. STI measures of ulcer, discharge, any symptom, and any STI were used as possible sexual outcome measures, with condom use and sexual and/or physical violence perpetration our behavioral outcome measures. Based upon our previous study we computed intraclass correlation (ICC) estimates between 0.00 and 0.01 for sexually transmitted diseases and 0.00-0.032 for behavioral measures. Given average camp sizes and ICC estimates we have inflated sample size estimates assuming simple random sampling with design effects ranging from 1.4 to 2.3. All sample estimates assumed an attrition of 20%. Given a sample size of 1955 sexually active males and 2808 total males in 54 camps we will have 80% power (2-sided, α=0.05) to detect the protective effect of the intervention (OR) of 0.32 for ulcer, 0.59 for discharge, 0.61 for any STI symptom, 0.50 for syphilis, and 0.66 for any STI. We will be able to detect protective effects of 0.74, 0.68 and 0.65 in condom use for those sexually active, for all males, and for sexual or physical violence perpetration in all males, respectively. Statistical power to detect mediation is expected to be high based on the simulation results of Fritz and MacKinnon where a total sample size of 539 was sufficient for .80 power to detect the most conservative simulated mediation effect.([Fritz & MacKinnon, 2007](#_ENREF_27))

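### Section 9.1.5 names propensity-score imputation for binary outcomes without running it by arm, which can shrink the treatment effect, and its relation to the non-response weights is not stated

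*Protocol*

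**What the plan says.** Section 9.1.5 first has the team examine the pattern of loss to follow-up and "apply an appropriate multiple imputation strategy if deemed necessary". It then names the methods: "We will use the propensity score method for multiple imputation and the Markov chain Monte Carlo approaches to multiple imputation of binary outcome data". It adds: "We will conduct sensitivity analyses that quantify the robustness of inferences to departures from underlying assumptions". It does not say which variables enter the imputation, whether it is done within arm, how camp is handled, or which model the Markov chain Monte Carlo (MCMC) approach uses.

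Section 9.1.3 compares the arms by odds ratio, at 12 months for behavioural outcomes and at 30 months for behavioural and STI outcomes, "using SAS SURVEYLOGISTIC version 9.2 to incorporate both the complex nature of sample selection and weighting". The weights include "non-response weights over each wave computed as the inverse of response rates".

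Section 9.1.1 allows for 20% attrition as a single figure, not by arm. Nothing states how the weights and the imputation relate.

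**The concern.** Propensity-score imputation groups men by their predicted probability of responding and fills each missing outcome from an observed man in the same group. It uses covariates only to predict response. If response is similar in the two arms, every group mixes arms, so a missing outcome in an intervention camp is filled partly from control men and the reverse. The imputed share of the data then carries little or no treatment effect. Both primary endpoints, STI and violence perpetration, are compared as odds ratios, so both are exposed.

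The second difficulty is that two adjustments are written down for the same loss to follow-up with no stated order. The choice of primary estimate could then be made after the data are seen, and the two can differ appreciably.

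**Working it through.** **1. The planned attrition (section 9.1.1).** Section 9.1.5 gives no figure of its own, so the 20% comes from the sample size.
- Men: 54 × 52 = 2808 and 54 × 36.2 = 1954.8, matching the stated 2808 and 1955.
- Camp size after 20% loss: 52 × 0.8 = 41.6. Design effect = 1 + (m − 1) × ICC, so 1 + 40.6 × 0.01 = 1.406 and 1 + 40.6 × 0.032 = 2.299, matching the stated 1.4 to 2.3.

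**2. Direct arithmetic, 20% missing at random in each arm, donors pooled over arms.** The control rate behind the power statement is not given. I take 41% for violence (ever perpetrated, section 1.7) and assume 10% for STI. The odds ratios of 0.65 and 0.66 are the detectable effects in section 9.1.1.
- Violence: control 0.4100; at OR 0.65, intervention 0.3112. Pooled donor rate: (0.4100 + 0.3112)/2 = 0.3606.
- Completed control: 0.8 × 0.4100 + 0.2 × 0.3606 = 0.4001. Completed intervention: 0.8 × 0.3112 + 0.2 × 0.3606 = 0.3211.
- Odds ratio: (0.3211/0.6789)/(0.4001/0.5999) = 0.71. Share of log OR kept: ln 0.709/ln 0.65 = 0.80.
- STI: 0.1000 and 0.0683, donor rate 0.0842, completed 0.0968 and 0.0715. Odds ratio 0.72; share kept 0.80.

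**3. Simulation with missingness depending on a covariate.** 8000 men, 150 replicates, 5 imputations, one covariate with effect 0.5 on the logit scale for both outcome and non-response, propensity quintiles with approximate Bayesian bootstrap, no clustering. Entries are the share of the full-data log OR kept (violence-like / STI-like).

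| Method | 20% missing in each arm | 25% control, 15% intervention |
|---|---|---|
| Propensity, pooled, arm not in response model | 78% / 76% | 78% / 76% |
| Propensity, pooled, arm in response model | 78% / 76% | 105% / 104% |
| Propensity, run within arm | 100% / 100% | 101% / 100% |
| Logistic imputation including arm | 100% / 100% | 101% / 100% |
| Inverse-response weights alone | 100–101% | 101% / 101% |
| Pooled propensity (arm not in response model) plus weights | 77% / 75% | 83% / 81% |

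With arm in the response model and the unequal loss reversed, so that the intervention arm loses more, the share kept falls to about 64 to 67%. Adding arm to the response model is therefore no cure: it changes nothing under equal attrition and makes the result depend on the direction of the imbalance.

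**4. What the loss means.** exp(0.78 × ln 0.65) = 0.71 and exp(0.76 × ln 0.66) = 0.73. For an effect planned at 80% power, two-sided 0.05, with the standard error held at its planned value, the expected z falls from 1.960 + 0.842 = 2.802 to 0.78 × 2.802 = 2.185. Power is then Φ(2.185 − 1.960) = 59%; at 0.76 it is 57%. The planned 80% already allows for attrition, so this drop reflects the attenuation alone. It is an illustration, not a forecast.

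**5. Weights and imputation side by side.** Section 9.1.3 builds the weights into the stated comparison. Section 9.1.5 makes imputation conditional and names its methods. Neither section refers to the other. Step 3 shows that weights laid over pooled propensity imputation do not repair it.

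**The case against.** The strongest reply is that section 9.1.5 is a sketch. Imputation happens only if judged necessary, the comparison actually fixed is the weighted one, and that comparison recovers the effect. Running by arm, choosing predictors and reflecting camp are commonly left to a statistical analysis plan, which is not at hand. All of this stands, and the absence of such detail is not the complaint. The complaint is that the protocol commits to a specific method that is poorly suited to estimating an arm effect unless one further condition is met. The planned sensitivity analyses are unspecified and do not change that commitment.

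Three stronger readings are tempting but unsupported.
- A reader might infer that the MCMC imputation assumes a normal model and yields non-binary values. The text says only that MCMC approaches are used for binary outcome data. If a normal model with rounding were used, the same simulation keeps 85 to 98%, but no such model is named.
- A reader might infer that men will be corrected twice. No section applies weights and imputation to the same analysis; the relation is simply undefined.
- A reader might infer that both primary odds ratios will be pulled toward 1. That holds only if imputation is used for the estimate and pooled over arms, and it also depends on the attrition pattern: with arm in the response model and more loss among controls, 104 to 105% was kept.

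**Conclusion.** The point holds in a conditional form. As written, section 9.1.5 permits a pooled propensity-score imputation that, at about 20% missing and equal attrition, removes roughly 20 to 25% of the log odds ratio (0.65 becomes about 0.71). Under unequal attrition the loss may be about a third or nil. Alternatives no harder to run, one of them already in section 9.1.3, keep about 100%. Separately, the protocol leaves open whether the weighted analysis or the imputation is primary.

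The size rests on the assumed control rates (41% and 10%), covariate effects of 0.5 on the logit scale, missingness explained by observed covariates, and no clustering in the simulation. Clustering would affect precision and therefore power, so the power figures are illustrative. The direction under pooling and equal attrition follows from the arithmetic in step 2 and does not depend on the simulation.

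**What to change.** - Replace the propensity-score method with outcome-model imputation: logistic, run separately by arm or with arm in the model, reflecting camp and using the available baseline covariates. At minimum, require that any propensity imputation be run within arm.
- For violence, add the baseline and 12-month values. For STI this is not possible in full: sections 3.3 and 6.4 test only half the men at baseline, and the Protocol Summary has no biological data at 12 months. Use behavioural covariates, and the baseline STI result only where it was measured.
- If MCMC is kept, state a model suited to binary data.
- Name either the weighted analysis or the imputation as primary and the other as sensitivity, and state that non-response weights are not applied to imputed records.
- Keep the planned sensitivity analyses for departures from the missing-data assumptions.

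The cost is a change of wording and a little more analysis work in standard software. No data collection changes.

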## 9.2 Qualitative Analysis Plan

Interviews will be conducted by local staff who have been hired and trained in qualitative research methods. All in-depth interviews with men from camps will be audio-taped, transcribed, translated, coded and computerized for analysis. Analysis will begin during data collection so that topics for further exploration can be incorporated into ongoing fieldwork. Qualitative data analysis consists of searching for patterns in data and conceptualizing ideas that help explain the presence of those patterns.([Bernard, 1995](#_ENREF_9)) Analysis of textual data will involve five steps: (1) reading for content; 2) deductive and inductive coding; 3) data display to identify emerging themes; 4) data reduction; and 5) interpretation.

# 10. ETHICS AND PROTECTION OF HUMAN SUBJECTS

## 10.1 Institutional Review

Prior to implementation of any study component at a site, the study strategy, informed consent and recruitment forms, and any other forms used with participants must be approved by the IRB at both UNC and in Tanzania. All form amendments and any other documents affecting the safety and welfare of study participants must be approved by both IRBs prior to implementation. The study site Principal Investigator is responsible for the preparation and submission of all documents and periodic reports required by an IRB.

## 10.2 Informed Consent

**Aim 1**

Enumerating and characterizing camps includes two stages of data collection. The first includes Community Informant interviews with community members in the fours wards of study; the second includes Camp Verification interviews with camp members. Since no personal data will be collected in this phase of the study, informed consent will not be collected.

**Aim 2**

HIV risk, gender-based violence perpetration, and their mediators will be assessed at baseline, 12 and 30 months. STI prevalence assessments will occur at baseline and 30 months. Participants selected to provide a biological specimen must have completed the behavioral assessment to be eligible. Separate written consent will be necessary for the behavioral and biological assessments. Potential participants will be excluded from participation based on an inability to provide informed consent. All consent documents will be stored in locked cabinets. Copies of the informed consent script will be provided to prospective participants to keep.

Research assistants will begin each interview by confirming the eligibility of participants. All eligible participants will then be read the informed consent script in Kiswahili and given the chance to ask questions or clarifications on what they are being asked to do in the study. Participants will acknowledge their consent by initialing the line for behavioral assessment and writing the date and their signature on the form.

Upon completion of the survey, participants selected for the biological assessment will meet with nurses who will administer the biological consent. Nurses will explain the purpose and procedure for blood and urine collection in private. Participants will acknowledge their consent by initialing the line for biological assessment.

Participants not selected for the biological assessment will have the opportunity to receive a symptomatic STI assessment with nurses. Nurses will explain the procedure for symptomatic STI assessment. Participants will acknowledge their consent by initialing the line for symptomatic STI assessment.

Written informed consent will be obtained from each participant in the qualitative sub-studies, prior to their participation. Participants will be provided with a copy of their consent form.

The host site has prior experience in obtaining informed consent for prevention trials within the cultural context. The informed consent procedure for this study has been designed to maximize understanding of potential risks. Consent forms will be translated into Kiswahili and piloted with 50 participants to ensure the script is understandable.

If there are cultural, literacy, or political reasons why signing the informed consent form is not appropriate, individuals will be allowed to mark consent forms with an “X”. At this point, any misunderstandings regarding procedures, risks, or benefits can be clarified. Individuals will be provided with information on how to contact the study staff to report adverse events associated with participation in any component of the study. Study staff will have been trained in the need to ensure individuals provide voluntary informed consent.

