## 3.3 Study Duration and Endpoints

The intervention will be implemented for two years, and the total duration of the trial will be 5 years. **The primary endpoints** are sexually transmitted infections including Neisseria gonorrhea (NG), Trichomonas vaginalis (TV), Chlamydia trachomatis (CT), and perpetration of physical or sexual violence against a sexual partner. A random sample of 50% of participating men will be flagged for an STI test at baseline to assess relative prevalence, and all men will be tested at endline. A test of relative prevalence at baseline will aid in establishing equivalency in the two arms; any lack of equivalency then will be controlled for appropriately at endline. All participants will complete a behavioral assessment at baseline, 12 months and 30 months to assess secondary objectives. **Secondary endpoints** are HIV risk and protective behaviors including: gender equity, alcohol and drug use, sexual relations and risk behavior, uptake of HIV counseling and testing; unprotected sexual intercourse; consistent condom use; delay of sexual debut; number of sexual partners, and sexual concurrency. **Key mediators** are hope, future orientation, social cohesion, collective efficacy, emotional distress, sexual networks, social support and social influence.

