## 4.5 Participant Withdrawal

Participants may voluntarily withdraw from the study at any time. If a participant chooses to withdraw during an assessment period they can choose not to have their assessment responses submitted to the study team.

Participants also may be withdrawn if the principal investigator, study sponsor, government or regulatory authorities, or site institutional review boards (IRBs) terminate the study prior to its planned end date. In such cases the Principal Investigator will review the reasons for withdrawal with the IRB and Protocol Biostatistician prior to participant notification. The Principal Investigator may decide to include data collected prior to participant withdrawal in study analyses.

Every reasonable effort will be made to complete a final assessment of participants who leave the study prior to the planned termination date. Study staff will record the reason(s) for all withdrawals from the study in participants’ study records.

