## 6.3 Baseline Behavioral Survey

Eligible and consenting camp members in the 60 selected camps will participate in a survey assessing socio-demographics, outcome variables and mediating variables (Appendix D). The questionnaires will be administered using CAPI by trained interviewers who are not intervention facilitators. The interview will last approximately 60 minutes. Interviews will take place in a central location within each ward, interviewers split between the four wards. Participants who appear influenced by drugs will be asked to return for an interview the next day.

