## 6.5 Follow-up Behavioral Assessments

At 12 months and 30 months a follow-up behavioral assessment will be conducted among eligible and consenting participants in order to assess outcome and mediating variables. We will use the same procedures described for the baseline assessment.

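### The survey-before-specimen rule names no survey round; followed literally at month 30, it costs the STI endpoint in men who refuse the survey but would still give urine

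*Protocol*

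**What the plan says.** Section 10.2 (Aim 2) first sets the timing: "STI prevalence assessments will occur at baseline and 30 months". The next sentence is the condition at issue: "Participants selected to provide a biological specimen must have completed the behavioral assessment to be eligible". The section then adds: "Separate written consent will be necessary for the behavioral and biological assessments". It also fixes the order of events: "Upon completion of the survey, participants selected for the biological assessment will meet with nurses who will administer the biological consent".

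On the survey, section 6.3 says: "The interview will last approximately 60 minutes". For the 12- and 30-month rounds, section 6.5 says: "We will use the same procedures described for the baseline assessment". Section 8.2.3 uses one form, of about an hour, at all three rounds.

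On testing, section 3.3 flags a random half of the men at baseline and says of the end of the trial that "all men will be tested at endline". Section 6.6 limits month-30 collection to men who are eligible and consent. Section 7.2 bases the NG, CT and TV endpoint on PCR of urine; blood is for HIV.

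**The concern.** At month 30 the condition ties two separate measurements together. A man who is willing to give urine but declines or stops an interview on violence, drugs and sexual partners would be turned away from the specimen. Refusing one assessment then forfeits both primary endpoints.

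The PCR result does not need his month-30 answers. His arm, camp and baseline covariates are already held. No later STI round is planned, so a result missed at this round is not recovered. The STI endpoint is the only primary endpoint that does not rest on self-report, and under this rule it takes on the non-response of the one that does. Men who stop such an interview may also differ in STI risk from those who finish it.

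**Working it through.** **1. Does the condition reach month 30?** The protocol gives no figure to reproduce here, so the passages are set side by side.

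- For: the sentence directly before the condition names both baseline and 30 months. Nurses give the biological consent only after the survey is complete. Section 6.5 carries baseline procedures forward, and section 8.2.3 uses the same form. Section 6.6 limits month-30 specimens to eligible men, and section 10.2 makes survey completion part of eligibility. Section 6.10 has nurses record completion of the endpoint survey as well as specimen provision. No section provides for a specimen-only visit.
- Against: the condition names no round. It speaks of men *selected* to give a specimen, and selection exists only at baseline, when half are sampled (sections 3.3 and 6.4).

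The same-visit reading at month 30 is the more natural one, but it is inferred.

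**2. Does survey-first have a purpose?** At baseline, yes. Section 6.4 samples half of the sexually active men, and sexual activity is a survey answer (Appendix D, Q1401). Section 6.6 has no such restriction at month 30.

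**3. How many results could be lost?** Inputs: 1249 men (Protocol Summary) and 20% attrition (section 9.1.1). The refusal or break-off rate is an assumption.

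- Men reached: 1249 × 0.80 = 999.
- 999 × 0.02 = 20; 999 × 0.05 = 50; 999 × 0.08 = 80.

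These are upper bounds at those rates. The rule costs a result only when a man refuses the survey and would have accepted the specimen. The 20% may also already include refusals.

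**4. What happens to power?** Section 9.1.1 plans on 1955 sexually active men in 54 camps, and this reproduces: 54 × 36.2 = 1954.8. The calculation uses ICC 0.01 (the top of the stated STI range), design effect 1 + (36.2 × retained fraction − 1) × 0.01, two-sided α of 0.05 and 80% power. The control prevalence and the extra specimen loss, in percentage points of enrolled men, are assumptions.

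| Extra loss | Men analysed | Detectable OR, 10% prevalence | Detectable OR, 20% prevalence |
| --- | --- | --- | --- |
| 0 | 1564 | 0.543 | 0.650 |
| 2 | 1525 | 0.540 | 0.647 |
| 5 | 1466 | 0.534 | 0.643 |
| 10 | 1369 | 0.523 | 0.634 |

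With 1249 men in 60 camps, a 5-point extra loss moves the detectable OR from 0.472 to 0.460 at 10% prevalence.

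**5. What bias could follow?** All inputs are assumptions: 8% STI prevalence in both arms (true OR 1.00), 16% among refusers, and a fraction r of reached men lost through the rule. Observed prevalence = (0.08 − 0.16r)/(1 − r).

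- Control, r = 0.03: 0.0752/0.97 = 0.0775.
- Intervention, r = 0.06: 0.0704/0.94 = 0.0749; OR = (0.0749/0.9251)/(0.0775/0.9225) = 0.963.
- Intervention, r = 0.08: 0.0672/0.92 = 0.0730; OR = 0.938.

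The direction comes from the assumption. Swapping the arms gives 1/0.963 = 1.04 and 1/0.938 = 1.07. Equal r in both arms leaves the OR at 1.00.

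**The case against.** The strongest objection is to the reading. Section 10.2 goes on to describe men who were not selected for the biological assessment, and no such men exist at month 30. The condition may therefore describe only the baseline sample, or the baseline survey may satisfy it at month 30. This stands as a real ambiguity. It does not remove the point, because field staff who apply the sentence as written, in the order that section 10.2 gives, would turn men away.

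The size is also open to challenge. Every rate is assumed, and the protocol does not suggest that refusal differs by arm. Learning which answers are desirable could as easily produce misreporting as refusal. Men are reimbursed for each visit (section 10.8). What counts as a completed survey is undefined, and at least one sensitive item may be skipped (Appendix D, Q1413), so a partial interview need not be an incomplete one. All of this stands, and it keeps the size unknown and probably small.

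Section 9.1.3 plans non-response weights and section 9.1.5 plans multiple imputation with sensitivity analyses. These mitigate the harm in part. They rest on assumptions about men whose specimens could simply have been collected.

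Three stronger readings are tempting, and the protocol does not support them:

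- A reader might infer from section 4.5 ("If a participant chooses to withdraw during an assessment period they can choose not to have their assessment responses submitted to the study team") that a continuing participant who withholds his answers forfeits his specimen. That sentence concerns men who are withdrawing and says nothing about specimens, so the point does not rest on it.
- A reader might see a flat contradiction with the statement in section 3.3 on testing all men. Section 6.6 qualifies that statement by eligibility and consent, so the two passages fit badly but do not strictly conflict.
- A reader might conclude that survey answers are never needed for the STI analysis. The STI sizing in section 9.1.1 uses sexually active men, and section 8.2.3 links laboratory codes to behavioral data.

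**Conclusion.** The point holds as a low-cost improvement, with medium confidence. Section 10.2 sets a collection rule that names no round and most naturally reaches month 30. Followed literally there, it forfeits the objective primary endpoint in enrolled men who would have given urine, although the biological consent is separate.

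The number of such men cannot be computed from the protocol. The figures of 20, 50 and 80 out of about 999 are ceilings at assumed refusal rates of 2%, 5% and 8%. The loss of power is small, and the bias under deliberately unequal assumed refusal is modest (a null OR seen as about 0.94 to 0.96). A reader might infer that the STI comparison is seriously underpowered or biased toward the intervention because of this rule. The protocol gives no refusal rate, no difference by arm and no STI risk among refusers, so that inference is not supported. An analysis method cannot recover the missing specimens, which is the reason to settle the rule before month-30 collection.

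**What to change.** In section 10.2, limit the survey-first condition to baseline and add a sentence such as: *At month 30, specimen collection is offered to every enrolled man under the separate biological consent, whether or not he completes the behavioral survey.* Adjust the month-30 flow so that a man who declines or stops the survey still meets the nurse. State that his result enters the STI analysis using his arm, camp and baseline covariates. If the condition was only ever meant for baseline, the same sentence settles it.

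The cost is a short amendment, with ethics approval where required, and a change to the nurses' sequence. No tests or staff are added, since testing of all men is already planned. The downside is that a few STI results will have no month-30 survey data. They drop out of any analysis that needs those answers, such as mediation models or an analysis restricted by current sexual activity.
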